In a follow-up intervention trial ([name], PI) funded by the Micronutrient Initiative and Conacyt (National Council of Science and Technology), Mexico, infants (n=600) born in the pregnancy study are being re-randomized to receive either multiple micronutrients or iron and vitamin A, daily from 3 to 24 months of age. Data collection on growth and development outcomes during the first 2 years of life is underway and is to be completed by the end of 2003. Many of the instruments will be useful for the proposed study (*see Appendix III*). Data on child growth, feeding practices, morbidity and development are being collected at several time points (3, 6, 9, 12, 18 and 24 months of age). In addition, data on micronutrient status and child-caregiver interaction are also being collected. Coverage rates for anthropometric measurements that are taken at home are high (>95%) at several time points among subjects who continue to receive supplementation. Coverage rates for measures of development (BSID-II) that are done at the study headquarters were around 70% at 12 and 18 months of age, with no incentives. Preliminary data indicate that at 1 year of age, 21.3% of children were stunted, *9.1% were anemic* and that approximately 9% and 17% of children have motor and mental development index scores, respectively, falling in the range of delayed development on the BSID-II[[145]](#endnote-145). Mean scores for the motor and mental development indices at 1 year of age were 88.7 + 7.9 (n=206) and 95 + 9.0 (n=207), respectively. *Preliminary analyses also show that Hb levels at 3 months of age and weight gain in the first year of life, were positive predictors of Hb levels at 1 year of age (n=230)[[146]](#endnote-146).*

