Sample size calculations are based on the expected effect size, power to detect those differences and level of significance. The expected effect sizes for key outcomes presented in Table 3 were calculated by dividing the minimum meaningful difference (d) that we wish to detect by the standard deviation (S.D.) using data from either the literature or from our preliminary studies in Mexico and Guatemala. Most of the effect sizes are small to medium (0.2 to 0.5) and the minimum sample sizes required to detect them using a two-tailed test and confidence level of 0.05 are shown in Table 4 at different levels of power (80-95%)[[192]](#endnote-192). The smallest effect sizes of interest are 0.22 S.D. for birth weight and 0.25 S.D. for motor and mental development at 18 months of age. Using a two tailed test and a significance level of =0.05, a final sample of 338 infants per group at the end of the study will have 90% power to detect an effect size of 0.25 S.D. or greater for all the major outcomes. This sample size will have 80% power to detect meaningful differences in birth weight (0.22 S.D) as we expect at least 393 births/group after accounting for loss to follow-up (see section D 1.5). The power calculations are also presented for single outcomes as well as for repeated measures of growth and development assuming correlations of 0.2. Due to budgetary constraints, blood and breast-milk samples will be obtained for a 30% sub-sample of 120 mother-infant pairs per group, which will have 95% power to detect expected effect sizes of 0.5 S.D.

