**Table 4: Minimum sample sizes by effect sizes, power and number of measurements**

| **Effect**  **size** | **Minimum Sample size per Group (2 tailed test, alpha=0.05, Correlation between repeated measurements=0.2)** | | | |
| --- | --- | --- | --- | --- |
| 80% Power  Time Points  1 2 3 | 85% Power  Time Points  1 2 3 | 90% Power  Time Points  1 2 3 | 95% Power  Time Points  1 2 3 |
| 0.2 | 393 237 185 | 450 271 211 | 526 317 247 | 651 391 305 |
| 0.3 | 175 106 83 | 201 121 95 | 234 142 110 | 290 175 136 |
| 0.4 | 99 60 47 | 113 69 54 | 132 80 63 | 163 99 77 |
| 0.5 | 64 39 31 | 73 45 35 | 85 52 41 | 105 64 50 |

**D.1.5. Recruitment of study subjects**: *(revised)*

*The power calculations dictate that a* minimum of 676 mother-child pairs should complete the study. We expect a 15% loss to follow up during pregnancy and a further 20% loss in infancy, and therefore need to recruit at least 994 pregnancies. *These estimates are conservative and include losses due to deaths and migrations out of the study area. All efforts however will be made to keep losses to a minimum. Attendance at routine prenatal and postnatal visits is already high in our study hospital and in addition we will be providing incentives to encourage participation.* Recent data indicate that IMSS General Hospital I has approximately 250 births/month, of which ~60% are predominantly breastfed until 3 months of age. The proportion of pregnancies that are high risk and therefore ineligible for inclusion is about 10%. Based on the above data, we expect to recruit at least 100 eligible pregnancies per month and therefore to complete recruitment in 10 months. The 30% subsample of mother-infant pairs for biochemical determinations will be selected at random.

**D.1.6. Time line:** *(revised)*

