**D.4.1. Overview of Statistical Approach**:

Generally, we will analyze outcomes from birth to 12 months of age among all children who reach that time point. In further analyses to be conducted in the subsample of children who are followed up until 18 months of age, missing interim endpoints will be imputed using multiple imputation procedures as described by Little and Rubin[[228]](#endnote-228). Effectiveness of randomization will be examined by comparing the two groups on key baseline characteristics. In the case of significant differences, group differences in outcomes will be examined with and without adjusting for these factors. Loss to follow-up is expected to be 20% to 18 months. We will assess selection bias by comparing baseline characteristics of subjects with and without the outcome measure of interest and control for any observed differences in the analyses.

All statistical analysis will be done using Statistical Analysis Software (SAS)[[229]](#endnote-229). A probability of p<0.05 will be considered statistically significant for all hypothesis testing. Assumptions of normality will be assessed using plots and tests of normality. Non-normal variables will be transformed or categorized as required. Descriptive data analysis will include examining the distributions of neurodevelopment, dietary intakes, anthropometric and PUFA status. Means, standard deviations, quartiles and median levels will be reported. Individual analytical hypotheses will be tested using the following general statistical techniques:

D.4.1.1. Outcomes measured at one time point: These are analyses which model outcomes collected at one point in time as a function of variables collected either cross-sectionally or longitudinally. For example, cognitive development at 18 months may be modeled as function of prenatal and postnatal growth, diet, and social confounding factors. These analyses can take several forms.

i. Analysis of Covariance will be used for comparison of means of two or more categories (e.g. supplement groups) adjusting for covariates, which may be either continuous or categorical.

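### The 18-month comparison is restricted to children seen at 18 months and imputes only their earlier visits, so infants lost after a 6- or 12-month Bayley test are left out although usable scores exist

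*Protocol*

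**What the plan says.** Protocol D.4.1 sets two rules. Up to one year, "we will analyze outcomes from birth to 12 months of age among all children who reach that time point". For the later analyses, "in the subsample of children who are followed up until 18 months of age, missing interim endpoints will be imputed". It adds "Loss to follow-up is expected to be 20% to 18 months", and handles selection by comparing baseline characteristics of children with and without the outcome and adjusting for differences found.

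D.2.2.1 gives the Bayley scales at 6, 12 and 18 months. D.4.2 writes the 18-month mental score as a regression on supplement group and confounders at that single time point. D.4.1.2 names GEE and mixed models (PROC MIXED) for repeated outcomes and lists motor and mental development among them, but does not say that either delivers the 18-month comparison.

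On numbers, D.1.4 states that "338 infants per group at the end of the study will have 90% power to detect an effect size of 0.25 S.D". D.1.5 says that a "minimum of 676 mother-child pairs should complete the study", that "We expect a 15% loss to follow up during pregnancy and a further 20% loss in infancy", and that the study will "need to recruit at least 994 pregnancies".

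Section E.10 calls child development the primary outcome, without an age. D.4.2 lists growth and development at 18 months among several principal outcomes.

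**The concern.** Being seen at 18 months is an event after randomisation. An analysis confined to children who reach it compares the arms as randomised only if those who leave are alike in the two arms. Baseline adjustment cannot deal with loss that is related to how a child developed after birth. For many children the protocol will hold direct information on that: earlier scores on the same scale. The stated rule uses imputation to fill earlier gaps for children whose 18-month score is known, and makes no use of the earlier scores of children whose 18-month score is missing.

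At stake is a biased estimate, in either direction, for a principal outcome and for the effect size of 0.25 SD on which the 338 per group rests. Power is not the main issue.

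**Working it through.** **Inputs.** From D.1.4 and Tables 3 and 4: SD 15 and target difference 3.75 points for the mental and motor indices, two-sided alpha 0.05, 338 completers per group, between-visit correlation 0.2. From D.1.5: 994 recruited, 15% loss in pregnancy, then 20% in infancy. Assumptions of this review, not in the protocol: correlations of 0.5 and 0.7, and the dependence of loss on the 12-month score.

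**The plan's own figures.**
- Sample size: 2 × (1.960 + 1.282)² / 0.25² = 336.3, so 337 per group against 338 stated. Power with 338 is 90.1%.
- Recruitment: 676 / (0.85 × 0.80) = 994.1, against 994 stated.

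Both reproduce.

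**Children left out at 18 months.**
- Births: 994 × 0.85 = 845, about 422 per group. (D.1.4 gives only a floor of 393 births per group.)
- Lost in infancy: 845 × 0.20 = 169, about 84 per group.
- Of all randomised, 1 − 676/994 = 32% are outside the 18-month analysis, counting losses in pregnancy.

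**Bias of the completers' difference.** Let z be the standardised 12-month score. Suppose that in one arm the log-odds of loss fall by s per SD of z, with the intercept set so that 20% are lost, and that in the other arm 20% are lost at random. The mean of z among that arm's completers then rises by m, and the bias in the 18-month difference is

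bias = correlation × 15 × m.

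Numerical integration gives m = 0.096 for s = 0.5 and m = 0.173 for s = 1.

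| Correlation | s = 0.5 | s = 1 |
|---|---|---|
| 0.2 (protocol) | 0.2 × 15 × 0.096 = 0.3 | 0.2 × 15 × 0.173 = 0.5 |
| 0.5 (assumed) | 0.5 × 15 × 0.096 = 0.7 | 0.5 × 15 × 0.173 = 1.3 |
| 0.7 (assumed) | 0.7 × 15 × 0.096 = 1.0 | 0.7 × 15 × 0.173 = 1.8 |

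The sign depends on the arm: if low scorers leave the placebo arm the difference shrinks; if they leave the DHA arm it grows.

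A simulation with 400,000 children per arm and a true difference of 3.75 agrees. With s = 0.5 in one arm, the completers' difference was 3.50 or 4.00 at correlation 0.2, 3.06 or 4.45 at 0.5, and 2.75 or 4.79 at 0.7. With s = 0.5 in both arms and 20% loss in each, it was 3.75 to 3.79, which is no material bias. Predicting the missing 18-month score by arm from the 12-month score gave 3.71 to 3.79 in all the one-arm cases. That is a best case, because every lost child was credited with a 12-month score.

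**Precision.** Using earlier scores of those lost, the variance per arm is proportional to (1 − r²)/338 + r²/422. The equivalent numbers per group are 340.7, 355.7 and 374.5 for r = 0.2, 0.5 and 0.7. Power moves from 0.901 to at most 0.904, 0.915 and 0.928.

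**The case against.** The best defence is that D.4.1.2 already plans longitudinal modelling of motor and mental development by supplement group, and a mixed model retains partly followed children. The restriction in D.4.1 is introduced as applying to further analyses. Imputing interim visits among children with an 18-month score also suits the hypothesis in D.1.1 about 18-month scores independent of earlier differences. This stands in part: the right tool is named, and interim imputation has a sensible use. But D.4.1 does not limit its rule to that hypothesis, D.4.2 models the 18-month score at one time point, and nothing says that the mixed model takes precedence.

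It also stands that the trial is double-blind with supplementation only in pregnancy, so strongly arm-specific loss is not the expected case. D.1.5 names deaths and migration among the losses. The protocol's only between-visit correlation is 0.2, which gives the smallest bias in the table.

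Two stronger readings are tempting. First, a reader might infer a power shortfall from the team's earlier study, where "Coverage rates for measures of development (BSID-II) that are done at the study headquarters were around 70% at 12 and 18 months of age". That sentence goes on to say that no incentives were given, whereas D.1.5 plans incentives here. Lower attendance would in any case be a retention problem, not a result of the analysis set. Second, a reader might suppose that selection runs in opposite directions in the two arms, which would enlarge the bias; the protocol offers no mechanism for that.

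**Conclusion.** The point holds as a defect in a stated rule, and should be fixed. The 18-month analyses leave out about 169 of about 845 births on the plan's own loss rate, and baseline adjustment is the only protection.

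The bias is conditional. It is close to zero if loss follows the same pattern in both arms. With loss tied to the 12-month score in one arm only, it is about 0.3 to 0.5 points at the protocol's correlation, and up to 1.0 to 1.8 points at an assumed 0.7, against a target of 3.75. The slopes and the two higher correlations are assumptions.

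The documents do not support three wider conclusions. The sample size is not wrong: the 338 per group are completers and recruitment is inflated for loss. Not every lost child has earlier Bayley scores: testing starts at 6 months, and the protocol does not split the 20% by age. And 18-month development is one of several principal outcomes, not the trial's sole main endpoint.

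**What to change.** State in D.4.1 that the 18-month mental, motor and growth comparisons include all live-born infants as randomised with any post-birth measurement. Estimate them with the mixed model already named in D.4.1.2, using every observed visit, arm-by-visit terms and baseline covariates, and reading the 18-month contrast from that model. An acceptable alternative is to impute the missing 18-month score itself, separately by arm, from earlier scores. Keep the completers' analysis as a sensitivity analysis, and bring the single-time-point equations in D.4.2 into line.

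The cost is wording and a small change to the SAS code; no extra data, visits or participants are needed. The downsides are reliance on data missing at random, little recovery for infants lost before 6 months, and only a small gain in power.

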**D.4.2. Analytical Plan:**

The principal outcome variables of interest will be birth outcomes (birth weight, length, maternal and newborn PUFA, neurodevelopment), breast milk PUFA levels, and child growth (weight, length, head circumference) and skinfold thickness) and development (cognitive and motor) at 18 months of age. In addition, weight and length gain from birth to 18 months of age, neurodevelopment at 1, 6 and 12 months, cognitive and motor development at 6 and 12 months and infant PUFA status at 1 and 3 months of age will also be examined. Preliminary descriptive analyses will be done to examine the distribution of the data and check for outliers, following which unadjusted comparisons of mean differences in length and weight and biochemical values will be made using Student's t test. The intervention groups will be compared on several baseline variables to ensure that randomization worked. Chi-square tests will be used to compare categorical variables and Student’s t test will be used to compare normally distributed continuous data. Following this, adjusted comparisons (using co-variance analysis)[[238]](#endnote-238) will be made if controlling for potential confounders is required using linear multiple regression for continuous variables and logistic regression for categorical variables[[239]](#endnote-239). In all cases, results will be presented before and after adjustment for confounding and testing of interactions.

Examples of some of the models for various hypotheses are presented below. For specific hypotheses 2a, using birth weight as the outcome of interest and general linear models regression analysis, we can test the following model:

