**Table 3: Expected effect sizes for key study outcomes at birth and during the postnatal period**

| **Study Outcomes** | **Birth** | | | **Postnatal (3-18 mo)** | | |
| --- | --- | --- | --- | --- | --- | --- |
|  | ***S.D.*** | ***Minimum difference (d)*** | ***Effect Size*** | ***S.D*** | ***Minimum difference (d)*** | ***Effect Size*** |
| **GrowthError: Reference source not found** |  |  |  |  |  |  |
| Weight (kg) | 0.45 | 0.1 | **0.22** | 1.0 | 0.3 | **0.30** |
| Length (cm) | 1.6 | 0.5 | **0.31** | 3.0 | 1.0 | **0.33** |
| Head Circumference (cm) | 2.0 | 0.5 | **0.25** | 1.5 | 0.5 | **0.33** |
| Gestational Age (d) | 7.0 | 2.0 | **0.29** | - | - | **-** |
| **Development Error: Reference source not found***.****Error: Reference source not found*** |  |  |  |  |  |  |
| Brazelton Score | 1.0 | 0.8 | **0.80** | - | - | **-** |
| Fagan Test | - | - | **-** | 2.7 | 2.00 | **0.74** |
| Mental Development Index | - | - | **-** | 15 | 3.75 | **0.25** |
| Motor Development Index | - | - | **-** | 15 | 3.75 | **0.25** |
| **DHA statusError: Reference source not found*,Error: Reference source not found*** |  |  |  |  |  |  |
| Maternal blood***** | 1.0 | 0.50 | **0.5** | 1.0 | 0.50 | **0.50** |
| Infant blood***** | 1.0 | 0.50 | **0.5** | 1.0 | 0.50 | **0.50** |
| Breast milk (% TFA) | **-** | **-** | **-** | 0.08 | 0.04 | **0.50** |

**plasma phospholipid DHA levels expressed as % total fatty acids (TFA)*

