weekly basis to distribute supplements and monitor compliance. *These workers will have a minimum qualification of having completed high school and will be trained to provide referrals for health care if required.* We expect about 100 - 400 women in the study per month and each worker will cover approximately 40-50 women. A team of 4*-5* trained nurses will obtain all baseline measurements (anthropometry, sociodemographic characteristics and obstetric history, diet, blood samples) at recruitment. They will also collect similar data for infants as well as blood and breast milk samples from mothers and *assist in measuring visual and auditory evoked potentials* and monitoring the birth outcomes to be collected as part of routine hospital procedures. All infant measurements will be done at the study headquarters in the IMSS General Hospital I. Mothers will be scheduled to bring their infants at 1, 3, 6, 9, 12 and 18 months, at which time growth and neurodevelopment outcomes will be measured. The total contact time per mother-infant pair is expected to range from 1-2 hours per visit of which the contact time for the infant ranges from 30 minutes at 9 months to 90 and 110 minutes at 12 and 18 months of age, respectively. The date of each assessment will be calculated based on birth date, plus or minus 7 days. A team of 3 trained psychologists will conduct all neurodevelopment and psychological measurements at the study headquarters. These include maternal intelligence at recruitment and the infant neurodevelopment outcomes, namely Neonatal Behavioural Assessment Scale (NBAS), Fagan and Bayley tests of motor and mental development (see section D. 2.2.1. for details). Approximately 4-5 infants will be scheduled daily (6 days a week) to be measured by the study nurse and psychologist. *Finally, two trained social workers will collect data on home environment during home visits at 6 and 12 months of age and at the study headquarters at 18 month of age.* Other study personnel will include an assistant who will coordinate all appointments and follow-up for data collection. Data entry operators (2) and lab assistants (1) will assist in data entry and cleaning and handling and analysis of biological samples at INSP.

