#### D.2.2.2. Maternal and Child Anthropometry (*revised)*: Maternal anthropometry will be obtained at recruitment and will include height, weight, mid-arm circumference, and triceps and subscapular skinfold thickness using standard procedures**[[203]](#endnote-203)** by trained workers. Details of maternal weight gain during pregnancy will be obtained from medical records. Weights will be recorded to the nearest 0.1 kg and heights to the nearest 0.5 cm. Length, weight and head circumference of the infants will be measured at birth and at 1, 3, 6, 9, 12 and 18 months of age using standard procedures. Data collectors will be trained in anthropometric techniques, and regular standardizations will be carried out. Measurement of accuracy and precision for all anthropometric measurements will be done using methods recommended by Lohman et al (1988)Error: Reference source not found. The scale will be calibrated twice daily with a known reference weight. All data collection will be done at the study headquarters and will be obtained in duplicate by the same data collector. Children will be weighed using a pediatric weighing scale with a precision of 10 g. Infants will be weighed without clothing at birth and with a minimum of clothing (e.g., undershirt, underpants or dry diaper) for subsequent measurements. The weight of clothing will be adjusted for using a second set of clothing. Recumbent length will be measured using a baby-board (UNICEF, Copenhagen, Denmark). Measurements will be read to the nearest 0.1 cm. Weight-for-age and length-for-age z scores will be calculated using the National Center for Health Statistics reference data**[[204]](#endnote-204)**. Head circumference will be measured at the largest occipitofrontal circumference to the nearest 0.1 cm with a non-stretchable tape.

D.2.2.3. Gestational Age and Birth Outcomes *(revised):* Details of birth outcomes (type of delivery, sex, livebirth, etc) will be obtained from hospital records and will be verified by interview in a 10% sub-sample. Gestational age will be determined at birth using Ballard’s method[[205]](#endnote-205).

D.2.2.4. Long Chain Polyunsaturated Fatty Acid Status (Maternal and Infant): *(revised)*

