***3a. Length (18 mo) = Constant + β 1 (Supplement)+ β2 (Other confounding)* *+ β3  (Supplement * other confounding)***

***3b. Mental development ( 18 mo) = Constant + β1 (Supplement)+ β 2 (Other confounding)* *+***

***β3  (Supplement * other confounding)***

Similar models can be specified to test the hypotheses stated under specific aims 1 & 4, for example that breast milk PUFA levels and infant PUFA status at 1 month of age will be higher in the intervention group compared to ‘control’ group. Mean values of breast milk and blood levels of DHA will be used as the dependent variables. Since some outcomes will also be defined as dichotomous outcomes, some of the hypotheses will also be tested using logistic regression. For example, if the dependent variable for specific hypothesis 3a is prevalence of stunting at 18 months of age that is defined using cut-offs for height/age Z score (HAZ), the model will be as follows:

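### Infant sex and exact age at measurement are recorded but not prespecified as covariates, so the postnatal growth comparisons give up a little precision at no saving

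*Protocol*

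**What the plan says.** All references are to the Protocol.

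- **First step of the analysis (D.4.2).** "unadjusted comparisons of mean differences in length and weight and biochemical values will be made using" Student's t test.
- **Models (D.4.2).** Attained size is the outcome, for example "3a. Length (18 mo) = Constant + β 1 (Supplement)+ β2 (Other confounding"), plus a supplement-by-confounder interaction.
- **Adjustment (D.4.1, D.4.2).** The groups are compared at baseline. D.4.1 calls for analyses with and without adjustment where they differ significantly. D.4.2 makes adjusted comparisons conditional on confounder control being needed, and then says results will be shown both before and after adjustment.
- **Covariates (D.4.1.2).** The examples are socioeconomic status, maternal BMI, intelligence and home environment. Infant sex and age at measurement are not among them.
- **Data available.** Infant sex comes from hospital records (D.2.2.3). Visits follow the rule "The date of each assessment will be calculated based on birth date, plus or minus 7 days" (D.2.1). Standardised scores are also planned: "Weight-for-age and length-for-age z scores will be calculated using the National Center for Health Statistics reference data" (D.2.2.2). The analysis section mentions them only in its stunting examples, with height-for-age cut at -2.
- **Principal growth outcomes (D.4.2).** These are size at birth and size at 18 months. Size at 1, 3, 6, 9 and 12 months belongs to hypothesis 3a but is not on the principal list.

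**The concern.** The adjustment rule is aimed at confounding, that is, at imbalance between the groups. Precision is a different matter. A factor that predicts the outcome strongly adds to the residual variance even when it is perfectly balanced, and putting it in the model removes that variance. Infant sex is such a factor for weight, length and head circumference. Randomisation will usually balance it, so a rule triggered by imbalance will usually leave it out. Exact age at the visit works the same way while growth is fast. At stake is the width of the confidence intervals for the DHA effect on growth. D.1.2 itself argues that small effects at one age may matter, and D.4.2 plans interaction tests, which need more precision than main effects.

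**Working it through.** **The plan's own figures.** For a standardised difference of 0.25, D.1.4 uses a "two-tailed test and confidence level of 0.05" and states that "a final sample of 338 infants per group at the end of the study will have 90% power to detect an effect size".
- n per group = 2(1.960 + 1.282)²/0.25² = 337, against 338 stated.
- Power at 338: 0.25 × √(338/2) = 3.25; 3.25 − 1.96 = 1.29; 90.1%. The figure reproduces.
- Recruitment: 676/(0.85 × 0.80) = 994, as stated.

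**Inputs from Table 3 (3–18 months).** Weight SD 1.0 kg, difference 0.3 kg; length SD 3.0 cm, difference 1.0 cm; head circumference SD 1.5 cm, difference 0.5 cm. Section E.9 expects half the children to be girls.

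**Assumed, because the Protocol does not give them.** Sex differences at 18 months of 0.4–0.8 kg and 1.0–2.0 cm; growth at 18 months of 0.15–0.30 kg and 0.8–1.2 cm per month; at 1 month, a gain of 25–40 g/day and an SD of 0.45–0.60 kg; visit ages uniform across the window.

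**Share of variance due to sex at 18 months**, (D/2)²/SD²:
- Weight: 0.2²/1.0² = 4%; 0.4²/1.0² = 16%.
- Length: 0.5²/3.0² = 2.8%; 1.0²/3.0² = 11.1%.

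**Share due to the visit window**, (growth rate × SD of age)²/SD², where the SD of age is 14/√12 = 4.04 days = 0.133 month:
- Weight at 18 months: (0.30 × 0.133)²/1.0² = 0.16% at most.
- Length at 18 months: (1.2 × 0.133)²/3.0² = 0.28% at most.
- Weight at 1 month: (25 × 4.04)²/600² = 2.8%; (40 × 4.04)²/450² = 12.9%.

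**Interval narrowing from removing the sex share at 18 months**, 1 − √(1 − share):
- Weight: 2.0% to 8.3%.
- Length: 1.4% to 5.7%.

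**Power and sample size at the Table 3 differences (removing sex and window):**

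| Outcome, 18 months | Power at 338, unadjusted | Power at 338, adjusted | n per group for 90%, unadjusted | n per group for 90%, adjusted |
|---|---|---|---|---|
| Weight, 0.3 kg | 97.4% | 97.8–98.9% | 234 | 196–225 |
| Length, 1.0 cm | 99.1% | 99.3–99.6% | 190 | 168–184 |

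Head circumference has the same standardised difference as length (0.5/1.5 = 0.33), so unadjusted power is again 99.1%.

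**Side check on the -2 cut.** Take the 21.3% stunted at 12 months in the investigators' earlier trial. Under normality, a shift of one third of an SD lowers this to 12.9%. Power at 338 per group is then about 82%, against 99% for the same shift on the continuous scale.

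**The case against.** Several points on the other side stand.

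- The t test is only the opening step. Adjusted models follow, their confounding term is open, and both the models and the covariate list are offered as examples. Sex and age could be included. A full covariate list is often left to the SAP, which was not available here. What remains is that nothing in the Protocol directs their inclusion, and the stated reason for adjusting would normally not be met.
- The Table 3 SDs are in raw units, so the sample size seems already to absorb sex variance. The trial is not short of power for growth at the differences it was planned on.
- Raw kg and cm are a valid scale. They match hypothesis 3a and Table 3.

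A reader might infer more than the text supports:

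- **That z-scores will be used only when cut at -2.** This rests on passages labelled as examples. D.4.1.1 allows linear models for any continuous growth indicator.
- **That the visit window matters throughout.** At 18 months, the principal postnatal time point for growth, it is under 0.3% of variance. Size at birth has no visit window.
- **That every growth measurement from 1 to 18 months is a principal outcome.** D.4.2 restricts the principal list to birth and 18 months.

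**Conclusion.** The point holds as a modest improvement in efficiency. The stated unadjusted test, with adjustment conditional on confounding, leaves known variation in the error term: about 4–16% of variance for weight and 3–11% for length at 18 months, nearly all of it from sex. Removing it would narrow the 18-month intervals by about 1% to 8% and add at most about 1.5 percentage points of power. Exact age adds something useful only at the earliest visits. The treatment estimate is unbiased and its type I error is unaffected either way.

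The shares depend on sex differences and growth rates that the Protocol does not give. They also depend on Table 3 SDs that pool 3–18 months. If the SD at a single age is smaller, both the shares and the starting power are higher. The 1-month figure is the least certain, because Table 3 gives no SD for that age.

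**What to change.** In D.4.2, state that every model of postnatal weight, length and head circumference includes infant sex and exact age in days at measurement as main effects, whatever the baseline comparison shows. Report the supplement effect in kg and cm, and keep the unadjusted difference for description. Two details need care:

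- Main effects should be specified because the models as printed also cross the supplement with the confounding term. Sex entered that way would change what β1 means.
- Age should be counted from birth and not corrected for gestation, because hypothesis 2a expects DHA to lengthen gestation.

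Continuous weight-for-age and length-for-age z-scores, already planned, may be analysed as an equivalent alternative or alongside the -2 cut. No z-score is planned for head circumference, so the covariates are needed there in any case.

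The cost is a sentence or two of wording. Sex and visit date are already collected, and sex is fixed before supplementation begins at 20–24 weeks, so it is a safe covariate.
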